### 6.2. Secondary endpoints

The domain-specific secondary outcome measures are:

Functional Status: will be measured at baseline and 90 days, using the PROMIS Physical Function – for Mobility Aid Users-SF. The Patient-Reported Outcomes Measurement Information System (PROMIS™) provides item banks that offer the potential for PRO measurement that is efficient (minimizes item number without compromising reliability) flexible (enables optional use of interchangeable items), and precise (has minimal error in estimate) measurement of

commonly-studied PROs. PROMIS item banks and their short forms provide evidence they are reliable and precise measures of generic symptoms and functional reports comparable to legacy instruments.

Health-related Quality of Life: will be measured at baseline and 90 days, using the Quality of Life Enjoyment and Satisfaction Questionnaire-SF. The Quality of Life Enjoyment and Satisfaction Questionnaire (Q-LES-Q) is a self-report measure designed to enable investigators to easily obtain sensitive measures of the degree of enjoyment and satisfaction experienced by subjects in various areas of daily functioning.

Transition to Hospice: will be assessed via claims data at 90 days to see if members transitioned to hospice care during the course of the study.

Emergent outpatient utilization: will be assessed via claims data at 90 days for a count of urgent outpatient visits for study participants.

Readmissions: will be assessed via claims data at day 7, 30, and 90 for any inpatient admissions after index admission, and whether readmission hospital was the same as index hospital.

Mortality: will be assessed via claims data at 90 days to see if and when the member/participant passes away.

## 7. TRIAL CONDUCT

### 7.1. Data collection

Quantitative data will be collected from several sources. Self-report assessments will be gathered at baseline and 90 days post discharge using REDCap Cloud, a secure data collection platform. Clinical data, additional patient demographic/descriptive information, and health care utilization data will be extracted from electronic health records and payer claims at baseline and 90-days. These data collection procedures have been used previously by our site teams (e.g., successfully retaining over 80% of participants in other large-scale studies). For individuals who withdraw from the study, data will be retained up to the point of study withdrawal.

Qualitative telephone interviews will be conducted to understand patient or caregiver intervention-related experiences. We will conduct the interviews as soon as possible following the 90-day follow-up to maximize participants recall related to involvement in the study. We will conduct interviews with 120 patients (30 patients from each of the 4 intervention arms). If a patient is unable to participate in an interview due to medical complexity, we will attempt to interview his/her primary caregiver. All audio recordings of interviews will be transcribed by experienced qualitative researchers and de-identified. We will use a unique study ID to label all study materials related to participation with a tracking log as

the only link to identifying information. Transcripts will be stored on a secure cloud-based environment approved by UPMC.

We will use the NVivo 12 (QSR International, Australia) platform for data analysis. A constant comparative thematic content approach will be used to analyze the qualitative data. Our qualitative analysis will be iterative and will take place over the course of the qualitative data collection period. For example, we will review transcripts from the first few patient interviews to begin developing a codebook and to make needed modifications to our interview guide for subsequent interviews. A separate codebook will be developed for each interview type (i.e., patient, intervention providers, primary care physicians) with the input of the Co-Investigators and the Stakeholder Advisory Board. We will assess inter-rater reliability using percent agreement and kappa scores. Upon acceptable interrater reliability, the qualitative research team will thematically code all qualitative documents.

## 7.2. *Blinding*

All study staff will be blinded to the adaptive intervention arm randomization probabilities. Study Co-Principal Investigators, Co-Investigators, and employed (non-consultant) statisticians will be blinded to the participant enrollment totals per named intervention arm. Teams caring for the patients (e.g., primary care physicians) will be unblinded to the interventions. All study staff will be completely unblinded after data collection is complete.

## 8. STATISTICAL ANALYSIS PLAN

### 8.1. *Statistical Objectives*

The following objectives and endpoints are relevant to the final statistical analysis of the ACCOMPLISH trial.

#### Primary analyses

- For Aim #1, the primary analyses will be to compare PDHD between the 5 study arms (STS and the 4 experimental intervention arms):
  - **Aim 1a:** Efficacy will be evaluated by comparing PDHD between the STS arm and each of the 4 experimental arms, adjusting for illness severity (mechanical ventilation + vasopressors) and discharge location (whether patient went to SNF prior to home) and accounting for multiple comparisons
  - **Aim 1b:** Superiority of each experimental arm over the others will be evaluated by calculating the posterior probability that PDHD for each arm is greater than the others, adjusting for illness severity

(mechanical ventilation + vasopressors) and discharge location (whether patient went to SNF prior to home).

## Secondary analyses

- To compare each intervention arm to STS, and to each other, with respect to mortality and PDHD among survivors.
- To determine the effects of each intervention arm and STS on secondary endpoints:
  - Functional status as measured by the PROMIS Physical Function—for Mobility Aid Users
  - Health-related Quality of Life (HQL) as measured by the Quality of Life Enjoyment and Satisfaction Questionnaire-SF (QLESQ-SF)
  - Transition to Hospice. Defined as whether the patient transitioned to hospice care.
  - Emergent outpatient care utilization. Defined as the count of urgent outpatient visits (ED visits and urgent visits).
  - Readmission. Defined as subsequent admission after index admission.
  - Mortality. Whether a patient dies during the first 90 days post discharge to home
- To explore potential heterogeneity of treatment effect

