#### 8.5.2. Extending the proportional odds model

To assess the proportional odds assumption around the lower end of the distribution, we propose the following non-proportional model in Equation (2):

$$\text{logit}(\gamma_{i,j}) = \alpha_j - (X_{i1}(\theta_{1,k} + \theta_{2,k}X_{i2} + \theta_{3,k}X_{i3} + \delta_kX_{i2}X_{i3}) + \beta_1Z_{i1} + \beta_2Z_{i2} + W_{i,COV} \boldsymbol{\kappa}), \quad k = -1, \geq 0. \#(2)$$

where we allow the treatment effect to vary for death ( $k = -1$ ) and stay constant across the home-days distribution (0-90). The effects for strata are constant across the full scale, -1:90.

This proposed model results in the probability of death for patients on STS equal to:

$$\Pr(Y_i = -1) = \text{logit}^{-1}(\alpha_{-1} - (\beta_1Z_{i1} + \beta_2Z_{i2} + W_{i,COV} \boldsymbol{\kappa}))$$

And the probability of death for patients on a treated arm:

$$\Pr(Y_i = -1) = \text{logit}^{-1}(\alpha_{-1} - (X_{i1}(\theta_{1,-1} + \theta_{2,-1}X_{i2} + \theta_{3,-1}X_{i3} + \delta_{-1}X_{i2}X_{i3}) + \beta_1Z_{i1} + \beta_2Z_{i2} + W_{i,COV} \boldsymbol{\kappa})).$$

Then the remainder of the 90-day home days scale can be described using the usual proportional odds shift, for

$j = 1, \dots, 89$ :

$$\Pr(Y_i \leq j) = \text{logit}^{-1}(\alpha_j - (X_{i1}(\theta_{1,\geq 0} + \theta_{2,\geq 0}X_{i2} + \theta_{3,\geq 0}X_{i3} + \delta_{\geq 0}X_{i2}X_{i3}) + \beta_1Z_{i1} + \beta_2Z_{i2} + W_{i,COV} \boldsymbol{\kappa})).$$

The priors will be the same as specified in Section 8.3.3 for each level of the log-odds treatment effects,  $\theta_k$ .

The qualitative interpretation of this model will be similar to the primary analysis model above; however, this formulation will allow us to assess how these interventions impact mortality versus the time at home.

Analyses of mortality and PDHD among survivors from the model in equation (2) will be considered separate secondary analyses. See Section 8.9.3 below.

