### 8.9.3. Final analysis of mortality and PDHD among survivors

Analysis of mortality and PDHD among survivors will be conducted jointly via the model in Section 8.5.2. This model relaxes the proportional odds assumption, allowing for the effect of interventions on mortality to be independent of the effect on PDHD among survivors. From this model, we will estimate the following posterior probabilities:

- Posterior probability of superiority of each active arm over STS with respect to probability of survival to 90 days
- Posterior probability that each active arm is superior to the other active arms with respect to probability of survival to 90 days
- Posterior probability of superiority of each active arm over STS with respect to PDHD among survivors
- Posterior probability that each active arm is superior to the other active arms with respect to PDHD among survivors

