#### 8.9.5. Final analysis of ordinal outcomes truncated by death

PROMIS and HRQoL are continuous outcomes collected around day 90 after discharge conditional on survival. Similarly, number of emergency visits by day 90 depends on having 90 days of follow up to be comparable between different treatment arms. Thus, to avoid selection bias we will analyze of these 3 outcomes using a similar composite outcome approach used for the primary outcome, wherein death before day 90 will be treated as the worst outcome on an ordinal scale otherwise consisting of the natural values taken by these variables. For PROMIS and HRQoL, which take positive values, deaths will be assigned a value of -1. For number of emergency visits by day 90, which also takes positive values up to the largest number of visits observed in the sample (K visits), deaths will be assigned a value of K+1. We will use a Bayesian proportional odds model to analyze these outcomes, similar to the approach of the primary analysis in 8.3.3. In our models, each unique value taken by these outcomes will receive its own intercept, a way of modeling continuous outcomes that is competitive with linear regression but which allows us to account for death. The linear predictor of our model will otherwise mimic that of the primary analysis in 8.3.3. From these models, we will estimate the following quantities:

- Posterior probability of superiority of each active arm over STS in terms of surviving with better functional outcomes (PROMIS and HRQoL), or fewer emergency visits within 90 days.

- Posterior probability of superiority of each active arm over all other active arms in terms of surviving with better functional outcomes (PROMIS or HRQoL), or fewer emergency visits within 90 days.

In the event that mortality rates are very small, or that the effect of interventions on mortality rates are very small, we will perform a survivors-only analysis of these endpoints, which is likely to be minimally biased under these conditions.

In these cases, we will analyze these endpoints among survivors to 90 days post-discharge. When modeling these endpoints, we will use Bayesian linear (for PROMIS and HRQoL) or generalized linear (number of emergency visits by 90 days) regression with uninformative priors. The linear predictors of these models will mimic that of the primary analysis in 8.3.3. From these models, we will estimate the following quantities:

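### The posterior probability of superiority on home days among survivors (8.1, 8.9.3) is not a treatment effect among survivors, whether read as conditional on survival or taken from equation (2) as printed

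*Combined protocol and SAP*

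**What the plan says.** The primary endpoint (6.1) scores death before day 90 as -1, so the primary analysis covers all randomized patients. Section 8.1 then adds a secondary objective: "To compare each intervention arm to STS, and to each other, with respect to mortality and PDHD among survivors". Section 8.5.2 gives its status: "Analyses of mortality and PDHD among survivors from the model in equation (2) will be considered separate secondary analyses".

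Equation (2) is fitted to the whole -1 to 90 scale. Its new feature is stated as "where we allow the treatment effect to vary for death", with a second set of effects (k>=0) for the rest of the scale. Both sets act on the cumulative probability Pr(Y<=j).

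Section 8.9.3 lists two kinds of result from this model, each also reported between active arms:
- for survival, the posterior chance that a given active arm beats STS in keeping patients alive at day 90
- for home days, a result named as follows: "Posterior probability of superiority of each active arm over STS with respect to PDHD among survivors"

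It describes the model in these terms: "This model relaxes the proportional odds assumption, allowing for the effect of interventions on mortality to be independent of the effect on PDHD among survivors". Section 12.6 likewise describes the odds ratios of its non-proportional scenarios as effects in survivors only.

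Section 8.9.5 takes a different line for PROMIS, quality of life and emergency visits: "Thus, to avoid selection bias we will analyze of these 3 outcomes using a similar composite outcome approach used for the primary outcome". It allows a survivors-only analysis of those outcomes under a condition: "In the event that mortality rates are very small, or that the effect of interventions on mortality rates are very small". It gives no numerical meaning to very small.

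**The concern.** Survival to day 90 is itself an outcome that 8.9.3 compares between arms. If an arm changes mortality, its survivors are a different mix of patients from the STS survivors, and a contrast between the two groups is no longer protected by randomization. The SAP recognises this in 8.9.5 but attaches no such condition or caveat to the survivors' home-days result in 8.9.3.

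Mortality is not negligible on the plan's own figures. Table 4 has 0.13 at baseline and 0.31 in the SNF stratum under OR 1.00, falling to 0.09 and 0.23 under the expected OR of 1.50.

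Readers will use the survivors' result to separate keeping people alive from keeping them at home. It has to mean what its label says.

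**Working it through.** **Inputs and method.** SAP Table 2 (0.133 death, then 0.005, 0.017, 0.017, 0.026, 0.042, 0.077, 0.228, 0.454), which sums to 0.999 and is rescaled to 1. The comparison is one active arm against STS, with equal arms, the nine collapsed levels and maximum likelihood on expected counts. There are no priors, strata or calendar-time terms. An OR above 1 favours the active arm, for death as well as for home days.

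**Step 1: reproduce the plan's tables (baseline, OR 1.5).**
- Table 6 shifts home days given survival. P(90 | alive) = 0.4545/0.8669 = 0.524, odds 1.102. Then 1.102 x 1.5 = 1.653, which is 0.623 of survivors, and 0.623 x 0.8669 = 0.540. Table 6 says 0.54.
- Table 4 shifts the unconditional scale. Odds of 90 days = 0.4545/0.5455 = 0.833. Then 0.833 x 1.5 = 1.250, which is 0.555. Mortality falls to 0.093. Table 4 says 0.55 and 0.09.

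Both are reproduced within rounding, and they are two different odds ratios. Equation (2) uses the Table 4 kind; the label in 8.9.3 and 12.6 describes the Table 6 kind.

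**Step 2: read the result as conditional on survival.** The documents do not say where patients saved or lost would fall on the scale, so this is assumed. Let mortality go from 0.133 to 0.093, with the saved patients spread over 0-79 days in proportion to Table 2 and nobody else affected.
- Share of survivors with 90 days: 0.4545/0.8669 = 0.524 becomes 0.4545/0.9069 = 0.501, a cut-specific OR of 0.91.
- Share with 80 or more: 0.6827/0.8669 = 0.788 becomes 0.6827/0.9069 = 0.753, an OR of 0.82.
- The proportional-odds fit to survivors gives 0.88. With 4 points lost instead of saved it gives 1.15.
- Range over 2 to 5 points and placement in 0-69 or 0-79 days: 0.85 to 0.94 (saved) and 1.07 to 1.22 (lost).
- If those patients resemble average survivors, the OR is exactly 1.00.

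**Step 3: read the result from equation (2).** The chance of being above level j is Pr(alive) x Pr(above j | alive). A k>=0 effect on Pr(Y<=j) therefore absorbs any change in survival. Take 4 points saved among average survivors. The share of survivors with 90 days stays at 0.524, but the share of all patients with 90 days rises from 0.4545 to 0.9069 x 0.524 = 0.475.

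| 4-point scenario | Survivors-only OR | Equation (2), home days | Equation (2), death |
|---|---|---|---|
| Saved, resemble average survivors | 1.00 | 1.14 | 1.17 |
| Saved, 0-79 days | 0.88 | 1.04 | 1.07 |
| Lost, 0-79 days | 1.15 | 0.96 | 0.94 |

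In both saved rows the survival OR put into the data is (0.907/0.093)/(0.867/0.133) = 1.50. The printed model isolates neither effect.

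**Step 4: test equation (2) on the 12.6 scenario.** Set the death OR to 1 and the k>=0 OR to 1.5. Under STS, Pr(Y<=19) = 0.1381, odds 0.160. Then 0.160/1.5 = 0.107, a probability of 0.097. Subtracting deaths, 0.097 - 0.133 = -0.037, a negative probability for 0-19 days. So equation (2) cannot represent no mortality effect together with this benefit. Fitted to the Table 6 distribution at OR 1.5, it returns a home-days OR of about 1.32 (true survivors' OR 1.5) and a death OR of about 1.30 (true 1.0). The primary model on the same data gives 1.32. The cause is that the 0-19 level holds only 0.005 of patients, so the death cut and the next cut nearly coincide and the two ORs are tied together.

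**The case against.** The strongest reply is that 8.9.3 does not subset to survivors. It fits equation (2) to everyone, deaths included, and shows survival beside home days. That is correct, and it disposes of a stronger reading. A reader might infer that the plan as written would rank an arm that saves frail patients below STS on home days, and an arm that loses them above it. A literal survivors-only comparison does that (0.88 and 1.15), but equation (2) gives 1.04 and 0.96, so the reversal did not occur under the printed model in the scenarios tested.

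A reader might also infer that the SAP declares superiority on this quantity. It does not. Section 8.9.3 only estimates posterior probabilities; the 0.991 threshold belongs to the primary analysis (8.9.1, 8.12) and the 0.9 rule to interim futility (8.8). Rates of crossing either threshold say nothing about 8.9.3.

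Three further replies have some force. Home days already has a death composite as its primary analysis, which is the safeguard 8.9.5 copies. The protocol's primary-outcome section expects only a small effect on time to death. The size of any selection effect depends on an assumed placement of the patients saved or lost, and can be zero.

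These points limit the consequences. They do not make the label correct: equation (2) gave 1.14 where the survivors' OR was 1.00, and 1.32 where it was 1.5.

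**Conclusion.** The concern holds for the secondary summary in 8.1 and 8.9.3. The reported probability is not the probability of a treatment effect on home days among survivors under either reading. As a conditional quantity it carries selection after randomization. As equation (2) is printed, it is neither conditional on survival nor independent of the mortality effect.

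The inconsistency with 8.9.5 rests on the text alone. The negative probability in step 4 follows from Table 2 and equation (2). The fitted ORs assume the collapsed scale, no priors or covariates, and, in steps 2 and 3, a stated placement of the patients saved or lost. The primary analysis, its threshold and the adaptive rules are not affected.

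**What to change.** 1. In 8.1 and 8.9.3, apply the 8.9.5 condition to home days, and state before unblinding what counts as very small (for example, a credible interval for the mortality risk difference lying within a named margin). Estimate that mortality effect from a model of death alone, because equation (2) returned a death OR of 1.30 where there was none.
2. When the condition is not met, label the survivors' home-day distribution descriptive, show it beside mortality, and make no superiority statement from it.
3. Either state that the k>=0 effect in equation (2) is a home-days effect in all randomized patients, or replace equation (2) with a model for home days conditional on survival. The second option needs the selection caveat and one bounding sensitivity analysis, for instance trimming the excess survivors of the better-surviving arm from the lowest home-day ranks.

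Cost: SAP wording and one extra table from data already being collected, plus refitting one secondary model if the conditional option is chosen. The downside is that one secondary statement becomes conditional.

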## 8.2. Intervention delivery

### 8.2.1. Intervention data

Data relating to the completion of intervention components will be summarized for each intervention arm separately. Intervention completion requires the cooperation of up to 3 components: automatic (computer generated) notifications, follow-up by the remote monitoring team (possibly in response to the automatic notification), and patient completion of follow-ups initiated automatically or by the response team.

The following RPM data will be collected:

- Number of RPM questionnaires sent to patients
- Number of RPM questionnaires completed by patients
- Number of yellow and red alerts sent to the monitoring team
- Number of yellow and red alerts addressed by the monitoring team within the appropriate time period
- Number of attempted in-person or virtual visits by the CRNP to the patient (enhanced team arms only)
- Number of medication reviews (enhanced team arms only)
- Number of documented advance directive/POLST discussions conducted (enhanced team arms only)

### 8.2.2. Intervention fidelity

Patients completing a minimum of intervention components (as outlined in section 8.2.1 above) will be considered as having followed the protocol for their intervention arm.

## 8.3. Bayesian adaptive design elements

### 8.3.1. Statistical modeling

The primary analysis is a Bayesian ordinal logistic regression model that accounts for differences in the 90-day PDHD depending on two patient strata that were significantly associated with outcomes in this population in a retrospective analysis of UPMC data (see Appendix): 1) illness severity (defined as patient needing ventilation or vasopressors), and 2) whether the patient was discharged to a SNF after they leave the hospital and prior to their discharge home. Treatment effects are modeled as a factorial where independent variables for RPM level (low or high) and type of team (standard or enhanced) are modeled with an interaction. The model assumes proportional treatment effects across the levels of the ordinal home days endpoint.

### 8.3.2. Bayesian ordinal logistic regression

The primary analysis employs a Bayesian cumulative logistic regression assuming proportional odds effects. Let  $Y_i \in \{-1, 0, 1, \dots, 89, 90\}$  be the primary ordinal 90-day home days endpoint for patient  $i$ . Let  $\gamma_{ij}$  denote the probability of patient  $i$  observing a home days endpoint of  $j$  or lower. For  $j = -1, \dots, 89$ , the primary analysis model is formulated as:

$$\begin{aligned} \text{logit}(\gamma_{i,j}) &= \alpha_j - (X_{i1}(\theta_1 + \theta_2 X_{i2} + \theta_3 X_{i3} \\ &\quad + \delta X_{i2} X_{i3}) + \beta_1 Z_{i1} + \beta_2 Z_{i2} + W_{i,COV} \boldsymbol{\kappa}) \end{aligned} \quad (1)$$

where  $\text{logit}(\gamma_{ij}) = \log\left(\frac{\gamma_{ij}}{1-\gamma_{ij}}\right)$  are the log odds of the probability that  $Y_i$  is less than  $j$ . The variables,  $X_{i1}, X_{i2}, X_{i3}$ , are indicators for treatment assignment, where  $X_{i1} = 1$  when randomized to one of the 4 care model interventions (interventions 2-5 above) and 0 when randomized to the STS arm,  $X_{i2} = 1$  when randomized to an intervention with RPM high and  $X_{i2} = 0$  for RPM low,  $X_{i3} = 1$  when randomized to an intervention with enhanced team and  $X_{i3} = 0$  for standard team. The model is formulated such that STS is considered the referent treatment and all parameters learned in the model are in relation to STS. The four care models are modeled as a factorial comprised of the level of RPM and type of team deployed.

The parameters  $\theta_1, \theta_2, \theta_3$  are log odds ratios for active interventions and the parameter,  $\delta$ , is an interaction effect between RPM high and enhanced team. We assume that the effects of each intervention are constant across strata and can be explained by a proportional log-odds ratio shift in the home days distribution. Each intervention's treatment effect is made up of components of the parameters, such that the treatment effect for RPM low/standard is equal to  $\theta_1$ , the effect for RPM high/standard is equal to  $\theta_1 + \theta_2$ , the effect for RPM low/enhanced is equal to  $\theta_1 + \theta_3$ , and the effect for RPM high/enhanced is equal to  $\theta_1 + \theta_2 + \theta_3 + \delta$ . We report these treatment effects as odds ratios, where  $OR_1 = \exp(\theta_1)$  is the odds ratio for RPM low/standard,  $OR_2 = \exp(\theta_1 + \theta_2)$  is the odds ratio for RPM high/standard,  $OR_3 = \exp(\theta_1 + \theta_3)$  is the odds ratio for RPM low/enhanced, and  $OR_4 = \exp(\theta_1 + \theta_2 + \theta_3 + \delta)$  is the odds ratio for RPM high/enhanced. The model is parameterized such that an odds ratio greater than 1 indicates that the care model is beneficial compared to STS.

The variables,  $Z_{i1}$  and  $Z_{i2}$ , are indicators of disease strata for patient  $i$ , where  $Z_{i1} = 1$  when a patient has severe illness (spent time on mechanical ventilation or vasopressors while hospitalized) and  $Z_{i1} = 0$  otherwise, and  $Z_{i2} = 1$  if patient  $i$  has been discharged to a SNF and  $Z_{i2} = 0$  if the patients is discharged immediately to home. With the above model, we assume that the underlying distribution of home days is different within each stratum, and that those differences can be explained by a proportional log-odds ratio shift in the home days distribution through the parameters,  $\beta_1$  and  $\beta_2$ .

Finally,  $p$  additional covariates,  $W_{iCOV}$ , are included in the model with parameters,  $\kappa$ .  $W_{COV}$  contain indicator variables for time at randomization, measured in buckets of 3-month intervals. The first time bucket (furthest in past) will be used as the referent in the model.

